##### Cohort III

Children with definite CP or high risk of CP. All participants are followed at ages 6, 12, 18 and 24 months and blood samples for whole genome sequencing is categorised as described below.

### Objectives

In the CP-EDIT cohort and in the GO-PLAY RCT a large dataset will be gathered. The focus is on eight areas related to implementation and perspectives of the families, and dissemination of data will be distributed in scientific publications according to the following areas:*MRI.* To evaluate MRI findings on early diagnostic MRI of participants in cohort II, who later will be categorized as either definite CP, high risk of CP, unclear or definitely not CP.*Genetics.* To evaluate genetic findings in early whole genome sequencing of participants in cohort III, which have definite CP or high risk of CP.*GMA implementation.* To assess the feasibility of applying The Prechtl Qualitative Assessment of General Movements in a multi-center Danish hospital setting.*Prediction of CP*. To determine the clinical utility of the MRI, HINE, HAI, and GMA to predict a confirmed diagnosis of CP at 24 months, in infants referred below 12 months of age.*GMA/HINE/MRI vs. HAI*. To compare diagnostic accuracy of sHAI and GMA/HINE/MRI*.**GO-PLAY.* To analyse the effect of the GO-PLAY intervention with early family-centred set-up for children with definite or high risk of CP. For 6 months these participants will receive regular follow-up in the home of the family with physiotherapist and occupational therapist will monitor and strengthen goal-based training.*Parents perspective on intervention.* To explore parents’ perspectives on barriers and facilitators involved in early intervention.*Parents perspective on early diagnosis.* To analyse interviews of parents’ perspectives of gains and concerns when having an early diagnosis of high risk of CP and how it affects parent-infant interaction.

#### Methods

*MRI*. Prospective cohort study. Descriptive analysis of MRI findings in the participants related to allocated group and outcome CP at age 24 months.*Genetics*. Prospective cohort study. Descriptive analysis of genetic findings in the participants related to allocated group and outcome CP at age 24 months.*GMA implementation.* Process evaluation of GMA implementation. Focus on fidelity, acceptability, and contextual factors influencing the feasibility of GMA.*Prediction of CP*. Prospective cohort study developing a transparent multivariable prediction model for individual diagnosis and prognosis of CP. We hypothesize that the MRI, HINE and GMA will have predictive validity equivalent to guideline recommendations and that the HAI score will be an important additive predictor to support early diagnosis of unilateral CP.Diagnostic test accuracy study. The aim is to determine the diagnostic accuracy (of sHAI for CP detection by using the interim diagnosis based on the combined assessment with MRI, GMA and/or HINE as a composite reference standard. The accuracy of sHAI will be assessed by measures of the test’s ability to detect the presence of high risk of CP.*GO-PLAY*. The primary aim of this trial is to compare the effectiveness of the GO-PLAY intervention, relative to the present standard of care, on the early motor development after 6 months in children with a definite or possible diagnosis of CP. The secondary aim is to compare the effectiveness of the GO-PLAY intervention, relative to the present standard of care, on parents’ ability to manage stress and anxiety and perceptions of health care services.*Parents perspectives on intervention*. Qualitative study based on focus groups of parents’ perspectives on barriers and facilitators in early intervention 1–3 months after participating in an early intervention program*Parents perspectives on early diagnosis*. Qualitative study based on individual semi-structured interviews of parents of infants with a diagnosis of high risk of CP. Parents are selected by purposive sampling and interviews are conducted in the home of the family 2–4 months after diagnosis of high risk of CP.

#### Primary and secondary outcome measures

*MRI.* Primary results are a description of MRI findings in children included in the CP-EDIT cohort II. The type of MRI findings will be analysed and related to history, presence and type of CP and age of the child. Secondary results are to analyse if cranial ultrasound and/or CT is correlated to MRI findings.*Genetics.* A complete overview of pathogenic/likely pathogenic variants identified in the CP-EDIT cohort III and thus providing an overview of the genetic findings in an unselected cohort of children with suspected CP in a clinical setting.*GMA implementation.* Fidelity outcomes: Multifaceted training packages provided: (a) number, (b) content, (c) physiotherapists´ perspectives on the utility of sessions. Proportion of high-risk infants screened with GMA. Interrater reliability between the GMA assessors. Acceptability outcomes: Number of GMA videos (a) sent by parents, (b) made by physiotherapists. Additionally, assessment of physiotherapists´ confidence in providing a GMA score. The contextual factors change during the implementation process, these will be continually examined through observations and if relevant interview with stakeholders.*Prediction of CP*. The primary outcome is a confirmed diagnosis of CP “yes vs. no” at age 24 months. For infants defined as definite CP or high risk of CP, diagnosis will be confirmed by a neuropaediatrician according to the SCPE criteria [33]. Key secondary outcome: Motor function will be classified according to the Gross Motor Function Classification System (GMFCS), categorized into five levels from walking without limitation (level I) to non-ambulatory function (levels IV and V) [34]. For infants defined as unclear or definitely not CP, medical records will be reviewed for diagnosis and walking ability at the age of 24 months.*Diagnostic test accuracy study*. Infants at risk of CP will be assessed with sHAI, a 6-item structured video recorded play session of 5 min of duration. The test is performed in the clinic and assessed by a certified HAI assessor. A combination of MRI, GMA and/or HINE will be applied as the gold standard i.e., the high risk of CP or CP diagnosis reference standard.*GO-PLAY*. Patients referred to CP-EDIT trial will be randomized to receive either GO-PLAY intervention or standard care plus assessments. The primary outcome is improvement in motor development evaluated by Peabody Developmental Motor Scale 2 (PDMS-2) from baseline (T0) to the end of intervention (endpoint T6, 6 months post baseline. Key secondary outcomes will be HAI when the child is ≤ 12 months at the end of intervention, AIMS, Gross Motor Function Measure (GMFM-66), Bayley Scale of Infant and Toddler development 4, cognitive part (BSID-4, cog) and parental well-being. Neither the families nor the therapists responsible for intervention are blinded to group allocation. All outcome assessors will be masked to group allocation. The therapists responsible for data collection at each assessment point are not involved in the intervention, are unbiased as to group allocation, and have no access to previous assessments.*Parents perspectives on intervention.* Data are analysed using thematic analysis. Results from this study may support clinicians in understanding the parent’s perspectives and customize early home-based intervention to address parents’ expectations, concerns and needs in the Danish health care system.*Parents perspectives on early diagnosis.* Data are analyzed using thematic analysis approach, supported by investigator triangulation [35]. Findings are expected to be presented as themes and subthemes. This study may help clinicians to support the parent-infant interaction and tailor counselling to address parents’ experiences, concerns, and needs.

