##### The 2^nd^ step

A child will be invited for the first assessment if the members of local steering group consider that the child has an increased risk of CP and parents’ consent is present. Children, participating in the assessment, will define Cohort II. Expected number of assessed children is 300.

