##### The 3^rd^ step

Participants from cohort II will be included in the follow-up study (cohort III who have high risk of CP or definitely CP) if they fulfil at least one of the requirements A or B:

A.any two of the following:A.1 Neuroimaging predictive of a motor disability including the involvement of one or more of the following structures: sensori-motor cortex, basal ganglia, posterior limb of the internal capsule, pyramidal tracts.A.2 GMA test with absent fidgety GMs at fidgety ageA.3 HINE scores < 57 at 3months or < 60 at 6months or < 63 at 9 months or < 66 at 12 monthsB.both of the following:B.1 Unilateral brain injury on neuroimaging (MRI or ultrasound) predictive of CPB.2 Clinical signs of asymmetry

The parents will be informed that a child has CP or has a high risk of CP. Approx. 160 children are expected to be included in the follow-up as high risk of CP or CP after the 1^st^ assessment.

Exclusion criteria from the 1^st^ step will be applied during the whole study. For example, if a child shows signs of progressive disorder at the age of 12 months and diagnosis becomes clear before the age of 18 months, the child will be moved from the CP-cohort (cohort III) to the non-CP group and not invited for further assessments in the CP-EDIT; the child will be classified as “no CP” at the age of 24 months.

Participants from cohort III from the two study sites at Aarhus and Aalborg hospitals will be included in the GO-PLAY randomized-controlled trial for children with CP or high risk of CP. Participation requires that parents talk sufficient Danish. We expect 60–80 participants in GO-PLAY.

After screening the definition of ‘Definitely CP’ encompasses participants that fulfil SCPE CP clinical criteria and guided by fulfilling the following: 4/5 for children < 5 months, and 3/4 for children ≥ 5 months of the following at screening.Delayed motor development without signs of neuromuscular disease (floppy infant, absent reflexes)GMA test with absent fidgety GMs at fidgety ageHINE scores < 57 at 3months or < 60 at 6months or < 63 at 9 months or < 66 at 12 monthsMRI or ultrasound of brain with a lesion in the abovementioned specific areasFocal neurological symptoms (hyperreflexia, clonus, dystonia, ataxia, intention tremor) or clinical signs of asymmetry

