### Sample size estimation

Sample size and statistical power has not been possible to estimate, since the variance of the outcomes is not known for many of the gathered data. Screening of 500 patients is realistic based on judgement by clinicians in the involved departments (e.g., by amount of neonatal admissions and referrals to neuropediatric clinic) and recruitment to previous studies in Denmark. Number of patients with CP is estimated from the Danish CP registry, indicating an incidence of 20 new patients from each of the 4 participating centers in the last years, therefore 160 is realistic to include in follow-up study, as children with high risk of CP also can be included, and a high interest from families to participate is anticipated. Distribution of participants in cohort II is estimated to derive from the neonatal pathway in 2/3 and from the infant pathway in 1/3 of cases.

The sample size for the GO-PLAY intervention trial has been calculated to be able to detect a large clinical effect (Cohen’s *d* = 0.8) corresponding to a difference between groups for PDMS-2 of 8 units, with greater than 80% statistical power at a 2-sided level of significance of 5%, comparing GO-PLAY (+ Standard of Care) with standard of care. Anticipating a standard deviation of 10.0, 26 patients are required in each of the two groups of primary interest (GO-PLAY versus standard of care). Accounting for 15% dropout rate, an estimated sample size is *n* = 60; approximately 30 participants per group.

Strategies for achieving adequate participant enrolment to reach target sample size includes dissemination to neuropaediatricians, and neonatologists, advertising on websites, and encouragement to disseminate knowledge about the study at paediatric departments in Denmark.

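### In the CP prediction study the 24-month diagnosis is verified differently according to a class set mainly by the predictors themselves, so CP missing from records can be counted as no CP

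*Protocol article*

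**What the plan says.** The Objectives section of the protocol article sets the aim: "To determine the clinical utility of the MRI, HINE, HAI, and GMA to predict a confirmed diagnosis of CP at 24 months". Under Primary and secondary outcome measures, the endpoint for this study is binary: "The primary outcome is a confirmed diagnosis of CP", yes or no, at age 24 months.

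The same section then gives two ways of establishing that endpoint:

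- For one part of the cohort: "For infants defined as definite CP or high risk of CP, diagnosis will be confirmed by a neuropaediatrician according to the SCPE criteria".
- For the rest, classed as unclear or definitely not CP: "medical records will be reviewed for diagnosis and walking ability at the age of 24 months".

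The 3rd step of the inclusion procedure decides which route an infant takes. Rule A requires "any two of the following": predictive neuroimaging, absent fidgety movements on GMA, or HINE below an age-specific cut-off. Rule B requires unilateral injury on imaging together with clinical asymmetry. A separate list for definite CP adds motor delay and focal signs to the same tests.

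The Cohort III section and Table 2 schedule visits at 6, 12, 18 and 24 months, with a clinical assessment of the CP diagnosis, for infants who enter follow-up. The article describes no examination for the record-review group at 24 months.

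**The concern.** When the tests being evaluated also decide how thoroughly the outcome is checked, the two parts of the cohort are measured against different reference standards. Here the definite or high-risk group has repeated visits and a specialist diagnosis on stated criteria. The unclear or not-CP group has whatever usual care has written down.

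The protocol's own text points to cases that may be recorded late. The Abstract refers to mild or ambiguous cases, and the Discussion says that unilateral CP often becomes evident later. The Introduction adds that MRI can be normal in CP. If such an infant is in the record-review group and has no recorded diagnosis by 24 months, a case missed by the entry rule is counted as a correct negative.

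At stake is how well the results of the prediction study can support clinical use of these tests. The two routes are written into the outcome definition, so this is not a detail left to an analysis plan.

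**Working it through.** **Group sizes.** The 2nd step states: "Expected number of assessed children is 300". The 3rd step expects about 160 in follow-up. That figure reproduces from Sample size estimation ("Number of patients with CP is estimated from the Danish CP registry"): 20 new patients per centre × 4 centres × 2 years of inclusion = 160. Record review therefore covers 300 − 160 = 140 infants, or 140/300 = 47%. The Abstract instead says that a subset of 300 with CP or at high risk is followed to two years. The two statements need reconciling.

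**Plan's own accuracy figure.** The article states no target sensitivity or precision for this study, so there is nothing to reproduce. What follows is illustration.

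**Formulas for the combined entry rule.** TP is the number of true CP cases in follow-up, FN the number of true CP cases among the 140, and r the share of those FN cases that record review finds.

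- True sensitivity = TP / (TP + FN)
- Apparent sensitivity = TP / (TP + r × FN)
- True NPV = (140 − FN) / 140; apparent NPV = (140 − r × FN) / 140

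**Example (assumed: 80% of the 160 have CP, so TP = 128; FN = 10).**

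| r | Sensitivity | NPV |
|---|---|---|
| 1 (no bias) | 128/138 = 92.8% | 130/140 = 92.9% |
| 0.9 | 128/137 = 93.4% | 131/140 = 93.6% |
| 0.5 | 128/133 = 96.2% | 135/140 = 96.4% |

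With FN = 20 and r = 0.5, a true 128/148 = 86.5% appears as 128/138 = 92.8%.

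**Wider range (assumed: 50% to 90% of the 160 have CP; 5% to 15% of the 140 have CP).**

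- Smallest case, TP = 144 and FN = 7: true 144/151 = 95.4%. At r = 0.9 it appears as 144/150.3 = 95.8% (0.4 points higher); at r = 0.5 as 144/147.5 = 97.6% (2.3 points from unrounded values).
- Largest case, TP = 80 and FN = 21: true 80/101 = 79.2%. At r = 0.9 it appears as 80/98.9 = 80.9% (1.7 points higher); at r = 0.5 as 80/90.5 = 88.4% (9.2 points).

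**Single tests.** Rule A needs two abnormal results, and GMA is done only below five months. An older infant without GMA therefore needs both imaging and HINE abnormal, unless rule B or the definite-CP list applies. An infant with one abnormal test can fall into record review, and a CP case missed there becomes a false positive for that test.

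Assume HINE is abnormal in 115 of the 128 cases and in all 10 others. True HINE sensitivity is (115 + 10)/138 = 90.6%. If records find half, it appears as (115 + 5)/(128 + 5) = 120/133 = 90.2%. In the limit where records find none, it is 115/128 = 89.8%. The bias is downward in this example.

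**HAI.** It is not part of the entry rule. Missed unilateral cases that HAI had flagged would count against it.

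**The case against.** The strongest reply is that the effect may be slight. The Abstract gives a mean age at diagnosis of 13 months in Denmark, and the Introduction cites 11 and 13 months from two national studies. Most CP should therefore be in the records by 24 months. The record-review infants were also examined by a neuropaediatrician at enrolment, and the review covers walking ability as well as diagnosis. This stands: it limits the likely size but does not make the two routes equivalent.

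Three stronger readings are tempting, and the documents do not support them.

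- A reader might infer that sensitivity, NPV and model discrimination are all inflated. The upward direction holds for the combined entry rule. The HINE example above shows that it can reverse for a single test, HAI is affected only indirectly, and the model combines separate predictors.
- A reader might push the illustration to a sensitivity of 100% for the entry rule, with every missed case absent from the records. That is implausible given the stated ages at diagnosis.
- A reader might infer that the confirming clinician is unblinded to the enrolment tests because no blinding is stated for that step. The article condenses a fuller protocol, so its silence here is not evidence of a defect.

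It can also be said that if the Abstract's 300 followed to two years were right, all assessed infants might be examined and the problem would disappear. The outcome section nevertheless assigns record review explicitly.

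**Conclusion.** The point holds as differential verification: the reference standard for 24-month CP depends on a class set mainly by three of the predictors under study. CP absent from the records at 24 months would be counted as no CP, which raises the apparent sensitivity and NPV of the combined entry rule. For individual tests, HAI and the multivariable model, the outcome is misclassified in a way related to the predictors, and the sign of the bias is not fixed.

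The size cannot be taken from the documents. Under the assumed ranges, the inflation for the entry rule is about 0.4 to 1.7 points if records find 90% of the missed cases, and about 2.3 to 9.2 points if they find half. If records find all of them, there is no bias from this source. Given the stated age at diagnosis, the lower end is quite possible. The change below is a cheap improvement and is worth making.

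**What to change.** 1. Look up every cohort II infant, whatever the class, in the Danish CP follow-up registry and the National Patient Registry (both already cited in the Introduction) at 24 months and again at a later fixed age. Use the later lookup as the outcome in a pre-specified sensitivity analysis.
2. Apply the SCPE criteria to the record-review group as far as the records allow, so that both groups are judged on the same definition.
3. Report accuracy and model performance over a stated range for the share of CP missed in the record-review group.
4. State that registry ascertainment may still differ by class, because followed infants reach the registries through study visits and the others through usual care. The lookup narrows and bounds the bias; it does not provide a reference independent of the tests.
5. Reconcile the 300 followed to two years in the Abstract with the roughly 160 in the 3rd step.

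The cost is a registry extract, possibly a data-permission amendment, and an additional analysis. No visits or procedures are added. The accuracy figures may turn out slightly less favourable.

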
#### Examination and intervention modalities

##### MRI

All included participants in cohort II with risk of CP (*n* = 300) will be offered MRI as quickly as possible or at term if premature. We expect that at least half of the children will have an existing diagnostic MRI scan or have been offered an MRI scan due to clinical indications. The rest of the included children will be referred to a diagnostic MRI scanning at 3 Tesla by the paediatricians in the CP-EDIT program. If the child is not able to cooperate for the duration of the scan, standard sedative, or general anaesthesia in accordance with regular MRI scan protocols of children will be used.

MRI scans will be described clinically by radiologists at the participating hospitals. The findings will be categorised according to SCPE criteria (Surveillance of Cerebral Palsy in Europe). In participants where ultrasound or CT scanning of the patients have already been performed as part of clinical follow-up, the results will be gathered, and additional MRI may be optional. Repeat MRI at ages 12 and 24 months will be optional for participants in cohort III as part of the complementary NIBS-CP project (NeuroImaging of Babies during natural Sleep to assess typical development and Cerebral Palsy), which may provide important biological information about myelination, microstructure, and connectivity of the white matter fibre tracts, as well as the metabolic profile, including markers of neuronal integrity and glial markers, of the brain tissue [36, 37].

##### Genetics

Blood samples will be obtained from participants with definite or high risk of CP (*n* = 160) upon inclusion in CP-EDIT cohort III after informed, written consent has been obtained by the parents. The parents will also be asked to provide a blood sample and written consent for genome sequencing (trio-analysis) to facilitate identification of de novo variants. Sequencing will be performed by the Danish Genome Center as part of their diagnostic data production for children with rare neurological diseases. A clinical geneticist and clinical laboratory geneticist will perform the data analysis and result interpretation. In cases of variants with uncertain significance a board may be consulted for interpretation of significance. The data will be analysed for copy number variation and structural variants as well as sequence variation in known disease genes and mitochondrial DNA. Results will be categorised as either: I) Pathogenic CP-explaining variant, II) Likely pathogenic CP-explaining variant, III) Variant of uncertain significance, IV) Likely benign variant, V) Benign variants (according to the ACMG guidelines) and VI) Pathogenic variant, non-CP disease. Only data from the proband will undergo a full analysis. All analysis will be performed in a diagnostic setting. De novo variants in gene with no known clinical association may be submitted to GeneMatcher (reference PMID: 26220891).

